### Randomization

This will be done by pharmacy according to block technique in 1:1 ratio to either lithium or placebo. Subjects and health care providers will be blinded to the allocation.

### Participant Withdrawal and Follow Up Consent

Subjects will be allowed to drop out of study anytime and if they decide to drop out of the study without completion, they will be asked if collection and analysis of their data could be continued.

### Safety Monitoring and Risk to Subjects

The risk for participants to take low dose lithium in short term is minimal and may include increased urine output, increase in serum sodium, and thirst. This will be explained to patients. Lithium has been used for mental disorders for decades in a dose up to 2,400 mg per day. Hence we do not anticipate that giving lithium for 3 days at a small dose will cause significant toxicity or harm to any patient. However, we will still monitor serum lithium levels to be certain of safety. There is no risk to matched controls who will only receive placebo treatment and standard of care as per cardiothoracic unit protocol. We will have an independent monitor for the study who will be a clinician not involved in recruitment and will be receiving serum lithium levels. The monitor will have access to patients' information who have been recruited for the study. If any provider involved or study monitor feel a safety concern at any time this will be promptly addressed.

### Data Collection

Demographic data (age, sex, race, ethnicity), comorbids, type of surgery, bypass time, aortic cross clamp time, complete blood count, renal function, electrolytes, lithium levels, urinalysis, urine protein and microalbumin, urine testing for AKI biomarkers such as neutrophil gelatinase-associated lipocalin (NGAL), kidney injury molecule-1 (KIM1), tissue inhibitor of metalloproteinases-2 (TIMP-2), and insulin-like growth factor-binding protein 7 (IGFBP7), [TIMP-2] × [IGFBP-7], use of renal replacement therapy type and days, days on mechanical ventilation, infections and death. Source of data is chart review of medical notes, laboratory tests and data will be collected for up to 60 days after surgery. Patients will be followed up in clinic at 6 months. Data will be collected into a web-based database designed to capture all visit information including medical history, results from laboratory analysis and adverse events. Baseline data and ongoing data collection as outlined in Table 1 will be obtained.

**Table 1 T1:** Clinical and laboratory data to be collected at various time points.

Baseline data at screening	Vital signs
	Complete blood count
	Serum chemistry
	^*^eGFR (CKD-EPI creatinine)
	Urinalysis
Perioperative and postoperative data	Vitals signs, intake and output
	Complete blood count
	Serum chemistry, renal function, estimated GFR
	Peak creatinine
	Novel AKI biomarkers: e.g. urinary TIMP-2, IGFBP7, and [TIMP-2] × [IGFBP-7]
	Days on mechanical ventilation
	Days on renal replacement therapy
	Sepsis episodes
	Death
Clinic visit at 6 months	Serum chemistry
	^*^eGFR (CKD-EPI creatinine)

* *Estimated Glomerular filtration rate (eGFR), chronic kidney disease- EPI creatinine (CKD-EPI) equation*.

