## Abstract

**Background:** Burgeoning pre-clinical evidence suggests that therapeutic targeting of glycogen synthase kinase 3β (GSK3β), a convergence point of multiple cellular protective signaling pathways, confers a beneficial effect on acute kidney injury (AKI) in experimental models. However, it remains unknown if GSK3β inhibition likewise mitigates AKI in humans. Cardiac surgery associated acute kidney injury (CSA-AKI) poses a significant challenge for clinicians and currently the only treatment available is general supportive measures. Lithium, an FDA approved mood stabilizer, is the best-known GSK3β inhibitor and has been safely used for over half a century as the first line regimen to treat bipolar affective disorders. This study attempts to examine the effectiveness of short term low dose lithium on CSA-AKI in human patients.

**Methods/Design:** This is a single center, prospective, randomized, double blinded, placebo controlled pilot study on patients undergoing cardiac surgery with cardiopulmonary bypass. Patients will be randomized to receive a small dose of lithium or placebo treatment for three consecutive days. Renal function will be measured via creatinine as well as novel AKI biomarkers. The primary outcome is incidence of AKI according to Acute Kidney Injury Network (AKIN) criteria, and secondary outcomes include receipt of new dialysis, days on dialysis, days on mechanical ventilation, infections within 1 month of surgery, and death within 90 days of surgery.

**Discussion:** As a standard selective inhibitor of GSK3β, lithium has been shown to exert a beneficial effect on tissue repair and regeneration upon acute injury in multiple organ systems, including the central nervous system and hematopoietic system. In experimental AKI, lithium at small doses is able to ameliorate AKI and promote kidney repair. Successful completion of this study will help to assess the effectiveness of lithium in CSA-AKI and could potentially pave the way for large-scale randomized trials to thoroughly evaluate the efficacy of this novel regimen for preventing AKI after cardiac surgery.

**Trial Registration:** This study was registered prospectively on the 17th February 2017 at ClinicalTrials.gov (NCT03056248, https://clinicaltrials.gov/ct2/show/NCT03056248?term=NCT03056248&draw=2&rank=1).

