### Study Endpoints

The primary endpoint of AKI is a composite of the occurrence of any of the following at 1-week from surgery: AKI based on the Acute Kidney Injury Network (AKIN) criteria. Other components include new onset dialysis at 30 or 90 days from surgery, and death within 90 days in lithium treated patients matched with controls.

Secondary endpoints of renal function/injury, post-operative therapy and infection will be monitored during the patient's hospital stay. Measures of renal function/injury include SCr, albumin to creatinine ratio, estimated glomerular filtration rate (eGFR), and urinary and urinary biomarkers; additionally, the number of days on renal replacement therapy (RRT), days on post-surgical mechanical ventilation, and infection will also be assessed as secondary outcomes.

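### Data collection ends at 60 days, but death and new dialysis are defined to 90 days and no ascertainment is planned for days 61-90

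*Protocol article*

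**What the plan says.** All references are to the protocol article.

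- **Collection period.** Data Collection lists, among other items, "use of renal replacement therapy type and days, days on mechanical ventilation, infections and death". The next sentence sets the limit: "Source of data is chart review of medical notes, laboratory tests and data will be collected for up to 60 days after surgery".
- **Later contact.** The same section adds: "Patients will be followed up in clinic at 6 months". Table 1 lists only serum chemistry and eGFR for that visit. Death, days on renal replacement therapy and sepsis episodes appear only in the perioperative and postoperative rows. Renal Function Measurement gives the purpose of the 6-month measurement as checking recovery from AKI. The study database is meant to "capture all visit information including medical history, results from laboratory analysis and adverse events".
- **Endpoint windows.** Study Endpoints includes in the primary composite "new onset dialysis at 30 or 90 days from surgery, and death within 90 days". The Abstract instead places new dialysis and death among the secondary outcomes, ending that list with "infections within 1 month of surgery, and death within 90 days of surgery".
- **Infection.** Study Endpoints says that "post-operative therapy and infection will be monitored during the" hospital stay.
- **Analyses.** Statistical Analysis compares a composite that includes dialysis and mortality between arms. For death and dialysis beyond 1 week it plans logistic regression, Kaplan-Meier curves with a log-rank comparison, and Cox models.

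**The concern.** An endpoint window can be analysed only as far as the data reach. Death and dialysis are defined to day 90, their collection is said to end at day 60, and nothing is scheduled in between that would record them. The analysis plan cannot repair this, because it cannot analyse events that the protocol does not collect.

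The consequence depends on the analysis. In a binary 90-day analysis, an unrecorded event on days 61-90 becomes a non-event and the 90-day risk is understated. In a time-to-event analysis censored at day 60, the estimate is sound up to day 60 but there is no 90-day figure.

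Infection raises a smaller, separate issue. If monitoring during the hospital stay is the operative rule, each patient's observation window equals length of stay. That is a post-randomisation variable which treatment may influence, so an arm discharged earlier would have less time in which to record infections.

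**Working it through.** **1. Windows side by side**

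| Outcome | Window as defined | Collection as described | Match |
|---|---|---|---|
| AKI | 1 week | up to 60 days | yes |
| New dialysis, 30-day version | 30 days | up to 60 days | yes |
| New dialysis, 90-day version | 90 days | up to 60 days | no |
| Death | 90 days | up to 60 days | no |
| Infection | 1 month (Abstract); hospital stay (Study Endpoints) | up to 60 days (Data Collection) | three periods, not reconciled |

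Uncovered part of the 90-day window: (90 - 60)/90 = 33% of the time. This is a share of time, not of risk.

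**2. Is 60 a slip for 90?** The text does not suggest so. Statistical Analysis also ends the longitudinal renal and biomarker analysis at 60 days.

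**3. Does the sample size depend on this?** The stated 182 reproduces from the AKI rate alone, using the confidence-limit formula with 20% in both arms and a 5-point difference:

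n per arm = z(0.80)² × 2p(1 - p)/d² = 0.8416² × 2 × 0.20 × 0.80/0.05² = 90.67, rounded up to 91, or 182 in total.

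Follow-up length does not enter, so 182 stands whichever way the windows are reconciled.

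**4. Dialysis events at stake.** The rates are the two in the Introduction, 1.4% and 2.7%. The article gives no time horizon for either, so they are used only for scale.

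- 182 × 0.014 = 2.5 events; 182 × 0.027 = 4.9 events, both arms together.
- The share falling after day 60 is not in the document. Assume 10% to 33%, where 33% corresponds to a constant hazard over 90 days.
- Low end: 2.55 × 0.10 = 0.25 missed. High end: 4.91 × 0.333 = 1.6 missed.

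**5. Deaths at stake.** The article gives no 90-day death rate for the trial population. Assuming 1% to 5%:

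- 182 × 0.01 = 1.8 and 182 × 0.05 = 9.1 deaths.
- With the same 10-33% share: 1.82 × 0.10 = 0.2 to 9.1 × 0.333 = 3.0 missed.

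**6. Weight of one event.** With 91 per arm, one event is 1/91 = 1.1 percentage points, against an overall dialysis rate of 1.4-2.7%.

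**The case against.** The case for a lighter reading has several parts.

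- **The 6-month visit could recover the data.** The database takes medical history and adverse events at visits, so day-90 status could be reconstructed for those who attend. This stands in part. A reader might infer that the 90-day endpoints cannot be ascertained at all, and the document does not support that. But neither vital status nor dialysis is listed for that visit, and attendance alone does not reveal deaths, non-attenders, or dialysis that began and stopped between days 61 and 90.
- **Kaplan-Meier estimates are not necessarily biased.** This stands. A reader might infer that the curves would be too low. That follows only if patients are carried as event-free past day 60, which no section says. With censoring at day 60, the log-rank and Cox comparisons remain valid over 0-60 days.
- **Infection collection does not plainly stop at discharge.** This stands. A reader of Study Endpoints alone might infer that infections after discharge are lost. Data Collection lists infections among the items gathered to 60 days, which contains the 1-month window. What remains is an inconsistency. The length-of-stay problem arises only if the hospital-stay wording governs.
- **The main comparison is untouched.** This stands. The tested hypothesis is AKI incidence within 1 week. Death and dialysis are components of the primary composite in Study Endpoints but secondary outcomes in the Abstract, and 30-day dialysis is fully covered.
- **Few events are likely to be missed.** This is fair: the upper figures require a constant hazard. Equally, with so few events expected, one missed event is not negligible.

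**Conclusion.** The point holds as a contradiction between stated windows: collection to 60 days against death to 90 days and dialysis to 30 or 90 days, with no planned ascertainment on days 61-90. It is more than an omission from a condensed article, because both windows are printed and they conflict.

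Its reach is limited to the 90-day death and dialysis results: the composite containing them, their binary analyses, and any 90-day reading of the survival analyses. The 1-week AKI test and the sample size are not affected.

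The likely loss is small in absolute terms, about 0.25-1.6 dialysis events and perhaps 0.2-3.0 deaths over both arms. The ranges rest on an assumed 10-33% of events falling after day 60 and, for deaths, on an assumed 1-5% risk. The dialysis range also treats the cited cohort rates as applicable here. The contradiction itself rests on none of these assumptions.

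The infection point is a wording conflict among three sections and is secondary.

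**What to change.** 1. **Death and dialysis.** Make one of two changes:
   - Amend Data Collection and Table 1 so that vital status and dialysis status, each with dates, are ascertained to day 90 for everyone randomised. Use a chart check or call, backed by a status-and-date question at the 6-month contact.
   - Keep 60 days, and restate death and dialysis as 60-day endpoints in the Abstract, Study Endpoints and Statistical Analysis.
2. **Infection.** State one fixed 30-day window, regardless of discharge, in the Abstract, Study Endpoints and Data Collection.

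The first option costs one extra chart check or call per patient and two dated status fields. It is best settled before follow-up closes, since prospective collection is easier than later reconstruction. The second option adds no data collection but gives up the 90-day results. The infection change is mainly wording, because collection to 60 days already covers 30. Neither option changes the sample size.

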### Renal Function Measurement

Baseline SCr is defined as the lowest Scr found in the last 3 months prior to encounter with cardiac surgery team. If there is not any prior value available and SCr remains stable at the time of patient encounter, then it will be deemed as baseline SCr. AKI will be defined as an abrupt (within 48 h) reduction in kidney function currently defined as an absolute increase in serum creatinine of more than or equal to 0.3 mg/dl (≥ 26.4 μmol/l), a percentage increase in serum creatinine of more than or equal to 50% (1.5-fold from baseline), or a reduction in urine output (documented oliguria of <0.5 ml/kg per hour for more than 6 h) (42). Patients will be deemed to have CSA-AKI if AKI occurs within 1 week of surgery. Studies have shown that the pattern of AKI recovery influenced the subsequent development of chronic kidney disease (CKD) (43). Thus we will also measure renal function at 6 months post-surgery to see if patients recovered from AKI.

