### Statistical Analysis

This randomized two-arm study is designed to test the null hypothesis of no difference in the primary endpoint of incidence of AKI as defined by AKIN criteria between the two treatment arms, placebo-control and lithium treatment. The primary endpoint will be analyzed on an intention-to-treat basis and patients will therefore be analyzed according to the assigned treatment group at study enrollment. The hypothesis of the study is based on the proportional incidence of AKI as follows:

$$\begin{array}{l} {\text{H}}_{\text{o}}:\lambda_{\text{lithium}}=\;\lambda_{\text{control}}\\ {\text{H}}_{\text{a}}:\lambda_{\text{lithium}}<\;\lambda_{\text{control}} \end{array}$$

Descriptive statistics and exploratory data analysis will be undertaken to summarize baseline characteristics between the control group and the lithium treated group to determine homogeneity and to identify potential differences that might be associated with incidence of AKI. Continuous data will be tested for goodness-of-fit to the normal distribution using Shapiro-Wilk test. If not normally distributed, the log-transformation of the data will be assessed for normality. Continuous data will be expressed as mean ± standard deviation (SD) of the untransformed or log-transformed version, or if neither are normally distributed, as median with interquartile range. Categorical data will be presented as frequency and percent. Comparisons of continuous data will be evaluated using two-sample *t*-tests or Wilcoxan rank sum test. For categorical variables, the chi-square test or, if frequencies are low (≤ 5), Fisher exact test will be used to compare groups. Statistical significance is defined as a *p*-value < 0.05.

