To examine the primary endpoint and test the study hypothesis for the effect of lithium on the incidence of AKI, contingency table analysis using chi-square will compare the proportion of AKI within the respective treatment groups. A predictive model that identifies baseline characteristics, including treatment assignment, associated with risk of AKI will be developed. Multivariate testing will use linear regression for continuous outcomes and logistic regression for dichotomous outcomes. Analysis comparing the placebo-control and lithium groups on each baseline characteristic, one at a time, using ANOVA with adjustment for age and sex will be performed. An adjusted logistic regression model based on the dichotomous outcome of occurrence or not of AKI will be further developed to identify characteristics significantly related to AKI. Composite endpoint events, consisting of the first occurrence of AKI, new onset dialysis, and cardiovascular/all-cause mortality, will be compared between treatment groups. Using appropriate uni- and multivariate methods, secondary outcome measures will be incorporated including assessments of renal function/injury such as SCr, NAGL, KIM1, urine TIMP-2, IGFBP7 and [TIMP-2] × [IGFBP-7], urine albumin Cr ratio, as well as indicators of post-operative course including days on mechanical ventilation, days on RRT and infection.

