Failure of clinical trials of new therapies for CSA-AKI is due, at least in part, to lack of a sensitive and specific marker for AKI. SCr is not a reliable marker for AKI. It is influenced by muscles mass, protein intake, volume status. Urine output also depends on confounding factors such as diuretics use, fluid administration and others. Hence, it is plausible that if we rely only on urine output or SCr we may miss some patients with relatively more short lived AKI, fluctuating volume status or low muscle mass. Some new biomarkers have been characterized in CSA-AKI and have shown to be helpful in the detection of early AKI (80). Urine TIMP-2 and IGFBP7 are new biomarkers for AKI and perform better than existing markers. They are both inducers of G1 cell-cycle arrest. In a study of 42 patients undergoing cardiac surgery, 38% developed AKI. Urinary [TIMP-2]·[IGFBP7] was found to be a sensitive and specific marker of AKI after cardiac surgery (81). In another study of patients undergoing CPB surgery the urinary [TIMP-2]·[IGFBP7] ratio was not able to detect AKI in the early postoperative period but did identify AKI patients on the first post-operative day (82). Based on existing evidence, we will also apply the NephroCheck test, an FDA-approved immunoassay test that measures the urinary concentrations of [TIMP-2] × [IGFBP-7], and measure urinary [TIMP-2]·[IGFBP7] on post-operative day 0, 1 and 2.

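### Low urine output alone counts as AKI in the primary endpoint, yet the protocol says lithium may increase urine output, so part of an apparent benefit could be urine volume rather than kidney protection

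*Protocol article*

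**What the plan says.** The Renal Function Measurement section of the protocol article defines AKI by three criteria, any one of which suffices: "an absolute increase in serum creatinine of more than or equal to 0.3 mg/dl", a rise of at least 50% (1.5-fold), "or a reduction in urine output (documented oliguria of <0.5 ml/kg per hour for more than 6 h"). It then sets the window: "Patients will be deemed to have CSA-AKI if AKI occurs within 1 week of surgery".

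The Statistical Analysis section tests the "null hypothesis of no difference in the primary endpoint of incidence of AKI as defined by AKIN criteria", with a directional alternative of less AKI on lithium. The method is that "contingency table analysis using chi-square will compare the proportion of AKI within the respective treatment groups". Study Endpoints adds dialysis and death to a composite, but AKI remains a component, so the point below is unaffected.

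Under Intervention, doses are given on the day of surgery and at 24-hour intervals twice more. Under Safety Monitoring and Risk to Subjects, the risks of this treatment are called minimal and "may include increased urine output, increase in serum sodium, and thirst". The Discussion concedes that "Urine output also depends on confounding factors such as diuretics use, fluid administration and others", but does not name the study drug among those factors. It describes the NephroCheck assay as one that "measures the urinary concentrations of [TIMP-2] × [IGFBP-7"].

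The article describes no analysis of AKI by creatinine alone and no breakdown of AKI events by qualifying criterion.

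**The concern.** A possible effect of the study drug acts directly on a measurement that can, by itself, make a patient an event or a non-event. A lithium patient who passes more urine can avoid the oliguria criterion while the kidney is no better off than on placebo. The shift goes in the direction of the alternative hypothesis. Diuretics and fluids, the confounders named in the Discussion, should balance on average between randomised arms. An effect of the allocated drug does not, and blinding cannot remove it.

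The decision at stake is whether to go on to a larger trial. Sample Size Estimation says the team will proceed only with evidence of efficacy, judged by a one-sided 80% confidence limit. That is a lenient bar, so a modest spurious difference can affect the decision.

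A smaller form of the issue touches the TIMP-2 × IGFBP-7 product: larger urine volume with unchanged excretion lowers a concentration.

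**Working it through.** **Inputs from Sample Size Estimation.** Control AKI rate 20%; clinically significant effect a 25% relative reduction (20% to 15%, 5 points); 91 per arm; one-sided 80% limit (z = 0.8416).

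**The plan's own figure.** n per arm = 2p(1−p)(z/d)² = 2 × 0.20 × 0.80 × (0.8416/0.05)² = 90.7, so 91 per arm and 182 in total. The stated size reproduces and is not in dispute.

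**Assumed inputs, given nowhere in the article.** f is the share of control AKI events that meet only the urine-output criterion. m is the share of those events that higher urine flow on lithium would mask.

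**Spurious difference.** With no effect on the kidney, the observed lithium rate is 0.20 × (1 − f·m), so the spurious relative reduction equals f·m. The chance that the one-sided 80% limit excludes zero is Φ(difference/SE − 0.8416), where SE = √[(p₁(1−p₁) + p₂(1−p₂))/91].

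| f | m | f·m | Control vs lithium | Expected events of 91 | Chance that 80% limit excludes zero |
|---|---|---|---|---|---|
| any | 0 | 0 | 20% vs 20% | 18.2 vs 18.2 | 20% |
| 0.10 | 0.25 | 0.025 | 20% vs 19.5% | 18.2 vs 17.7 | 22% |
| 0.10 | 0.5 | 0.05 | 20% vs 19% | 18.2 vs 17.3 | 25% |
| 0.25 | 0.5 | 0.125 | 20% vs 17.5% | 18.2 vs 15.9 | 34% |
| 0.50 | 0.5 | 0.25 | 20% vs 15% | 18.2 vs 13.7 | 52% |

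Example for the last row: SE = √[(0.16 + 0.1275)/91] = 0.0562; 0.05/0.0562 − 0.8416 = 0.048; Φ = 0.52. In that row the chance of a significant result in lithium's favour is 14% (two-sided 0.05) or 22% (one-sided 0.05).

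**Same scenarios, creatinine criteria only.** The spurious difference by this route is zero in every row, because urine volume does not directly enter either creatinine criterion.

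**What a creatinine-only definition would cost as primary.** If f = 0.25, the control rate falls to 15% and a 25% relative reduction is 3.75 points: 2 × 0.15 × 0.85 × (0.8416/0.0375)² = 128.4, so 129 per arm. If f = 0.50, the rate is 10% and the reduction 2.5 points: 2 × 0.10 × 0.90 × (0.8416/0.025)² = 204 per arm.

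**Biomarker dilution (assumed volumes, unchanged excretion).** A concentration scales as 1/V and a product of two as 1/V². A volume 10%, 20% or 50% larger lowers one concentration by 9%, 17% or 33%, and the product by 17%, 31% or 56%.

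**The case against.** The strongest reply has four parts.

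- **The drug effect is only a possibility.** A reader might infer that the protocol says lithium raises urine output. It says that it may, gives no size or frequency, and describes three doses at 1/3 to 1/4 of the standard psychiatric dose. This stands: the bias is a risk, not an established effect.
- **The direction is not certain.** The same sentence lists thirst and raised serum sodium. If these reflect fluid loss, creatinine could rise and add AKI events on lithium. This also stands as a possible partial offset.
- **Creatinine is already examined.** Serum creatinine and eGFR are secondary outcomes, percent change in creatinine is modelled, and Table 1 lists peak creatinine. A reader might infer that all the evidence would agree on a false benefit; these analyses show that it need not. But the check is only partial, because a comparison of creatinine values does not show which criterion produced the AKI events.
- **AKIN is a published definition, and the Discussion gives a reason for not relying on one marker.** This stands against replacing it. A creatinine-only primary would also undercut the 91 per arm, as shown above.

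On biomarkers, a reader might infer that all of them are read as raw concentrations. The article describes concentration only for the TIMP-2 × IGFBP-7 assay. For NGAL and KIM1 it is silent on scale, which an article may leave to the fuller documents.

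**Conclusion.** The point holds as a risk to interpretation. The AKI definition lets oliguria alone count, the protocol lists increased urine output as a possible effect of lithium, and dosing lies inside the AKI window. These three statements together mean that the primary comparison can favour lithium without renal benefit.

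The size cannot be derived from the article. Over the assumed range it runs from about half a percentage point (f·m = 0.025) to the full 5-point target (f·m = 0.25). At the upper end, the chance that the 80% limit excludes zero rises from 20% to about 52%. These figures assume a 20% control rate, 91 per arm, no kidney effect and no offset through creatinine.

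The documents do not support the stronger conclusion that a positive result would be an artefact, or that AKIN is the wrong primary definition. As described, though, the analysis could not show whether the bias was negligible or large. The biomarker issue is secondary and rests on the TIMP-2 × IGFBP-7 assay description.

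**What to change.** Keep AKIN as the primary definition and add the following before unblinding:

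1. A prespecified key sensitivity analysis of AKI by the two creatinine criteria only (≥0.3 mg/dl or ≥1.5-fold), with the same window, population and test as the primary.
2. A table of AKI events by qualifying criterion (creatinine only, urine output only, both) and by arm.
3. Urine output summarised by arm.
4. A rule that the creatinine-only result must agree in direction with the primary result before renal protection is claimed or a larger trial is pursued. Agreement in direction is a modest hurdle, since with no true effect it can occur by chance; it should be read with the table in item 2.
5. As a secondary point, an analysis of the urinary biomarkers indexed to urine creatinine, where urine creatinine is available on the same sample. The albumin-to-creatinine ratio already needs urine creatinine, but the article does not say that it is measured on the day 0 to 3 biomarker samples.

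Items 1 to 3 use data already listed for collection (renal function, peak creatinine, intake and output). The cost is a small amount of extra analysis. The creatinine-only analysis will have fewer events than the 91 per arm was sized for, and so less precision for the same 25% relative reduction; it should be reported as an estimate with its interval, not as a second powered test.
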